### **3.3 Preclinical Evidence for GS2**

Glucosafe, the predecessor of GS2, was a clinical research tool with focus on improving blood glucose control, in particular during the acute phase of the ICU stay, where insulin for blood glucose control is most needed. GS2 is intended for use as a clinical medical device, applicable for most ICU patients both during the acute phase and the recovery phase, where the focus on adequate nutrition is increased. This has necessitated modifications to turn Glucosafe into GS2. The modifications are listed and discussed in detail in GS2's investigator's brochure (GS2-IB).

Both preclinical and clinical testing of Glucosafe was made in the past. Due to the modifications, equivalence is not claimed between Glucosafe and GS2, but the closeness of Glucosafe's model to GS2's model and the fact that the prediction error of Glucosafe has been studied to some extent and in different cohorts (explained in Section 3.3.1), motivates us to consider evidence for Glucosafe as preclinical evidence for GS2. Moreover, Glucosafe's BG prediction error curve is used as a factor for early termination of the clinical trial should GS2 fail to reach the expected prediction accuracy (as explained in Section 2.9). We summarize the available preclinical and clinical testing in Sections 3.3.1 and 3.3.3.

#### **3.3.1 Preclinical testing of Glucosafe**

A review of the preclinical testing of Glucosafe has shown:

a) Glucosafe's physiological model can simulate the blood glucose data during normoglycaemia and during hyperglycaemia [28]. This ability is due to the saturation of insulin action incorporated in Glucosafe's physiological model [28, 29]. This gives a rationale for believing that Glucosafe's model may also be superior for simulating BG during changes in BG and insulin concentration.

b) Two retrospective analyses [30, 31] tested the ability of Glucosafe's physiological model to predict BG concentration of critically ill patients into the future and quantified the accuracy of these predictions in different patient cohorts and for different prediction time lengths. We found that the prediction error becomes larger the longer blood glucose is predicted into the future, as seen from the graphs in Figure 1 both on the left and right panel. We also found that there may be different prediction errors for different cohorts, as seen on the right panel of Figure 1. From Figure 1, we quantified the prediction error of Glucosafe's physiological model to be in the range of 10% to 17% for predictions of 1 hour into the future, and 17% to 26% for predictions of 2 hours into the future.

[figure not shown]

*Figure 1 Analysis of prediction error from retrospectively predicting BG with Glucosafe's physiological model. Left: The root mean square (RMS) of the natural logarithm of the BG prediction error is plotted against prediction time in hours on the x-axis [31]. Data are from 10 randomly selected trauma and/or neurologic ICU patients. Right: The RMS of the relative prediction error is plotted against prediction time, for two different physiological models and patient cohorts. The Glucosafe model is denoted "GS model" [30].*

### 3.3.2 Conclusion from the preclinical evidence for Glucosafe

Glucosafe's physiological model can simulate BG in different cohorts under normoglycaemic, hyperglycaemic, and hypoglycaemic conditions. Glucosafe predicts BG with good accuracy, but the prediction error depends on the prediction time. In different cohort, prediction errors ranged from 10% to 17% for predictions of 1 hour, 17%-26% for predictions of 2 hours, and 21%-29% for predictions of 3 hours.

### 3.3.3 Clinical evidence for Glucosafe

Glucosafe has been clinically studied in three prospective pilot studies. Two were published [32, 33] and the third study is described in the following abstract [34]. Although the studies are clinical, we consider them pre-clinical in relation to GS2, since the addition of advice on protein intake in GS2 makes Glucosafe and GS2 non-equivalent. The studies were conducted between 2009 and 2011 with ethics approval from the local ethics boards.

c) In the first of these studies, conducted in 2009 [32], 10 consecutively recruited hyperglycaemic patients (2 BG > 8 mmol/l or 1 BG > 10 mmol/l) from a neuro-trauma ICU were treated according to Glucosafe advice for 12-14 hours. Patients had an average APACHEII score of 12 (range 3-18), most with subarachnoid or intracranial haemorrhage. Hypoglycaemia (BG < 3.5 mmol/l) was not observed. Both mean BG and BG variability during the intervention period was lower ( $7.0 \pm 1.1$  mmol/l) compared to the 24h-preintervention period ( $8.6 \pm 2.4$  mmol/l;  $p < .01$ ) and also compared to the 24h-postintervention period ( $7.4 \pm 1.5$  mmol/l;  $p = .03$ ) (Figure 2). Nine of ten patients reached the normal BG target range (defined as 4.4-6.1 mmol/l in this study) after a mean of 5 hours with Glucosafe advice. The caregivers accepted 73% of Glucosafe advice unaltered, and the remaining were partially accepted.

[figure not shown]

Figure 2. Distribution of BG during 24h-preintervention (before), 12-14h-intervention (Glucosafe) and 24h-postintervention (after).

d) The second study [33] was planned as a randomized controlled trial of 40 consecutively enrolled patients in a neuro-trauma ICU, but was discontinued because organizational challenges at the clinical partner site made the successful completion of the trial unlikely. Data from 12 patients (6 intervention, 6 control group patients) were analysed, all with traumatic brain injury, polytrauma, or subarachnoid haemorrhage. Patients had an average SAPSII score of 39 (range 21-60).

Data were collected for four days. The BG target range 5-8 mmol/l. Nutritional targets were individually prescribed by the attending physician and were between 25-30 kcal/d per kg ideal body weight. The mean BG was significantly lower ( $7.0 \pm 1.2$  mmol/l) in Glucosafe patients than in control patients ( $8.0 \pm 1.2$  mmol/l). No adverse events including hypoglycaemia were reported in either group. In the intervention group, 170 (76%) measured BG values were in the 5-8 mmol/l target band, with the lowest BG value at 4.2 mmol/l. In the control group, 171 (51%) measured BG values were in the 5-8 mmol/l target band and the lowest BG was 4.0 mmol/l. The Glucosafe group was closer to isocaloric feeding ( $93.5 \pm 15\%$  of EE) than the control group ( $129.5 \pm 29.4\%$  of EE), but the difference was not significant.

e) In the third pilot study [34], Glucosafe's advice for insulin infusion was administered to 13 hyperglycaemic surgical and medical ICU patients and glycaemia was compared to the pre- and post-intervention days. The BG target range was 5-8.3 mmol/l. Nutrition was provided according to the department guidelines. Fig. 3 shows the cumulated BG measurements over the data collection periods.

[figure not shown]

Figure 3. Distribution of BG during 24h-preintervention (before), 12-14h-intervention (Glucosafe) and 24h-postintervention (after).

During Glucosafe intervention the mean and SD of BG ( $5.8 \pm 0.9$  mmol/l; N=99) was lower than during pre-intervention ( $7.8 \pm 1.8$  mmol/l; N=86) and during post-intervention ( $6.4 \pm 1.4$  mmol/l; N=56). No hypoglycaemic events occurred.

### 3.3.4 Summary of the clinical evidence for Glucosafe

The studies mentioned in Section 3.3.3 above showed that advice by Glucosafe lowered the mean BG and increased the time in the BG target range. In the three studies the BG target ranges were 4.4-7.7 mmol/l, 5-8 mmol/l and 5-8.3 mmol/l, respectively.

In study d, where Glucosafe was used to advice both on insulin and caloric intake, the advice from Glucosafe brought the caloric intake closer to the recommended isocaloric intake, where the caloric intake matches the estimated energy expenditure.

## 3.4 Clinical Evidence to Date for GS2

In the GS2-Clinical Evaluation Report, no clinical testing of GS2 or any equivalent medical device has been identified. Therefore, no claims are currently made for GS2. The performance and safety of GS2 will be assessed through a clinical trial for which a pre-market approval has been applied for at the relevant competent authority.

As mentioned in point 3.3 "Preclinical evidence for GS2", all preclinical tests were performed with Glucosafe, the predecessor of GS2. The predictive accuracy of GS2 will be confirmed by analysis of the historical control group before the prospective phase of the study is initiated.

GS2's predictions of the BG concentrations may be less accurate than assumed. The BG prediction error of GS2 is assumed to match to the error of the GS2 predecessor, Glucosafe (see Section 3.3). The assumed error curve is shown in Fig. 4 below, which was determined by several small retrospective studies [30, 31] of model-based predictions of BG in different ICU patient cohorts (not including ICU-Geneva patients). As with its predecessor Glucosafe, GS2 uses prediction error to calculate the maximum time until the next blood glucose measurement to keep the risk of hypoglycemia below the acceptable maximum risk level (see Section 8.1.1 for details). Thus, a larger prediction error shortens the time to the next measurement, which could ultimately increase the frequency of BG measurements to an unacceptable and undesirable level. From Fig. 4 it can be read that the RMS prediction error of Glucosafe was about 26% for predictions of BG 2 hours into the future. The RMS prediction error will be estimated from the historical control group and a new curve will be drawn to be compared with the curve in Fig. 4. It is expected that GS2 performs equally well or better than its predecessor. If the RMS prediction error of GS2 is greater for the historical control group, the sponsor will decide to discontinue the GS2 study. The cut-off point set to 2 hours is based on the frequency of BG measurements recommended by ICU-Geneva's glycaemic control policies (see Sect.8.1.2).

[figure not shown]

*Figure 4 Maximum acceptable RMS prediction error curve for predictions of BG in the historical control group. The curve is derived from pre-clinical evidence with GS2's predecessor, Glucosafe. For predictions 2 hours into the future, the curve allows the RMS prediction error to be at a maximum of 26%.*

### 3.5 Justification for the design of the clinical investigation

Reduction of hyper- and hypoglycaemia reduces mortality and adequate nutritional support reduces post-ICU weakness as well as ICU and post-ICU morbi-mortality, as discussed in sect. 3.1. The intended purpose of the study is therefore to assess whether GS2 safely and effectively can reduce hyper- and hypoglycaemia and can bring the achieved nutritional support closer to the nutritional guidelines. The achievement of these study objectives (sect. 4) will be evaluated through the calculation of a number of study outcomes (sect. 5), which will be used to make comparisons between the patients in:

- 1) GS2 intervention group
- 2) Control group
- 3) Historical control group (sect. 3.6)

### 3.6 Explanation for choice of comparator

In the GS2 intervention group the clinicians are advised by GS2 and in the control group the patients are treated in accordance with the department's guidelines. There may be a cross-over effect from the GS2 advice, which potentially may influence the clinicians' treatment of the patients in the control group. To be able to assess this cross-over effect a historical control group is included in the trial.

### 3.7 Risk evaluation (Risk-to-Benefits rationale)

A device risk analysis and risk assessment has been conducted according to EN ISO 14971. Risks were identified by class: General risks, software risks, usability risks and installation risks according to EN 14971, EN62304, EN62366-1 and EN14971, respectively. All identified risks related to the four events: Hypoglycaemia, hyperglycaemia, overfeeding or underfeeding. After mitigation of risks, all risks were minor, except two general risks, GR2 and GR3, both related to hypoglycaemia. These two risks therefore require justification.

The justification of **GR2**, as stated in the GS2-Risk Management Report, showed that the expected risk of a patient experiencing hypoglycaemia is 2%, which is smaller than the 5% reported in IIT trials in the control group and much smaller than what is reported for the intervention group. The risk of 2% depends on the setting Hypoglycaemia Risk Maximum (GS2- SDS03-Settings in Appendix 7.2). The Hypoglycaemia Risk Maximum is set to 0.05%. This is the risk that a given BG measurement, made at the due time calculated by GS2, is hypoglycaemic, as described in GS2-SDS06-BG prediction error and BG due time. Assuming an average of 40 BG measurements per patient, then the patients risk of hypoglycaemia can be estimated as  $0,05\% \cdot 40 = 2\%$ .

The justification of GR3, as stated in the GS2-Risk Management Report, showed that the occasional hazard of not recognizing a type 1 diabetes patient is outweighed for that patient by the expected medical benefit of using GS2.

The final Risk Management Report in the GS2-Risk Management File state that the GS2 software has a Class B safety classification and that after all possible efforts to mitigate risks only two unacceptable risks remained, both general risks and both justifiable.

Moreover, as GS2 only gives advice and cannot control directly the insulin management, the risk remains lower than with an autonomous software.

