| Design:                         | 
Randomized controlled study with an intervention group, a control group; a historical control group will also be studied:
 
 
- Intervention group: Glucosafe 2 is used until the patient is discharged from the ICU or for a maximal follow-up of 15 days or when he/she starts eating (voluntary feeding). Number of patients: 71
 
- Control group: Standard care according to local ICU protocols (Geneva-HUG). The maximal follow-up is of 15 days or when he/she starts eating (voluntary feeding). Number of patients: 71.
 
- Historical control group: retrospective data from a random sample of 71 patients exposed to the standard care regarding nutrition support and glycaemic control and recruited before the beginning of the pilot study in order to minimize the “cross-over” effects and to confirm the predictive accuracy of Glucosafe2. Historical controls’ data will be retrospectively harvested from the patients’ computerized record. They will be recruited within 2 years before the trial start.
 
 |
| Inclusion / exclusion criteria: | 
Inclusion criteria:
 
All patients <math>\geq 18</math> years old admitted in adult ICU- Geneva with
 
 
• An expected length of stay <math>\geq 72</math>h
 
• At least 1 blood glucose (BG) measurement <math>\geq 10</math> mmol/l or 2 BG measurement <math>\geq 8.5</math> mmol/l
 
• Informed Consent signed by the subject/ legal representative, except for patients in the historical control group
 
 
Exclusion criteria:
 
 
• Lack of legal consent or consent withdrawn, except for patients in the historical control group
 
• Pregnant or breast feeding
 
• Diabetic ketoacidosis or hyperosmolar state
 
• Oral feeding
 
• Fulminant hepatic failure
 
• Medically contraindicated to receive rapidly acting insulin by intravenous (iv) infusion or iv injection
 
                                                                                                                                             |

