## Calculation of due time for the next blood glucose measurement

GS2 uses the BG prediction error to calculate the maximum time until the next BG measurement is due. The purpose of this is to keep the hypoglycaemia risk at any time below the acceptable risk maximum of 0.05% per measurement, or 2% per patient (under the assumption that one patient has on average about 40 measurements taken, 2% is given by  $0.05\% \times 40$ ). The prediction error is a function of the prediction time, the longer the prediction, the larger is the "uncertainty" of the predicted BG, and thus the "uncertainty curve" has the shape of a "funnel", as can be seen in Fig. 7 above (light-pink shaded area beneath the thicker black line depicting the predicted BG in the upper left-hand plot).

A close-up of Fig. 7 with annotations in text is shown below. The time of the next measurement is when 1) the first time the lower edge of the uncertainty curve reaches the hypoglycaemia threshold, or 2) the next measurement is due according to local department rules, when that is sooner than 1).

[figure not shown]

A close-up of Fig.7 upper left-hand panel: The next BG measurement is due at 20:08, when the lower edge of the uncertainty area (light-pink shaded) the first time touches the hypoglycaemia threshold (dashed horizontal line) after the most recent BG measurement (red squares). The BG target range is depicted as light-green area, and each BG measurement shows the insulin sensitivity that was calculated at the time of the measurement.

In mathematical terms, the "uncertainty curve" at each time  $t$  for the predicted BG concentration is:

$$UC(t) = \exp(\ln \text{predicted BG}(t) + \text{Norm.Inv}(0.0005) * \ln PE(t))$$

where 0.0005 or 0.05% is the "Hypoglycaemia Risk Maximum" setting, i.e., the highest risk of hypoglycaemia deemed acceptable.  $\text{Norm.Inv}(0.0005) = -3.29$  is the inverse of the cumulative normal distribution.

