### 8.1.2 Control Intervention (standard/routine/comparator)

The current local protocols for glycaemia control and nutrition management will be used in the control group and in the historical control group for comparison.

After ICU admission, a BG measurement is performed. If glycaemia is in the accepted range (5.0-8.5 mmol/l) or spontaneously normal (4.0 to 5.5 mmol/l), no correction is proposed. In this case, a BG control should be done every 2 hours. In case BG measurements are twice  $> 8.5$  mmol/l, a new control is proposed in another sampling site. If the BG measurement is still  $> 8.5$  mmol/l, an IV insulin-therapy should be initiated following the local protocol. A further BG control should be done within the next 15-30 minutes until stability of the BG. Then, BG controls should be done every 2 hours. If BG measurement are  $< 4$  mmol/l, insulin-therapy should be stopped (if in progress) and a correction can be performed. A new control is done within 15 minutes. If the glycaemia is still under 4, a new correction is done. If the glycaemia is spent above 4, BG control are spaced to every 30 minutes. Then, when the glycaemia spent above 5, BG control are done every 2 hours. The algorithm of the local glycaemia control ICU protocol is presented in Figure 9.

[figure not shown]

Figure 9. Algorithm of the local glycaemia control ICU protocol (control and historical control group)

An estimation of caloric target is performed after the admission in the ICU. Then, if the patient stays more than 4 days and if the indirect calorimetry measurement is achievable, the measurement is performed, and the caloric target is adjusted. If gastro-intestinal tract is functional and there are no contraindications to enteral nutrition, it is started from day 1 with an appropriate solution regarding the pathologies and with an initial debit of 25 ml/h or 10 ml/h for a patient with severe shock (can be adapted according to tolerance). The 80-100% of the energy target need to be achieved at the end of day 3. If the energy target (80-100%) is not covered at day 4, a SPN (Supplemental Parenteral Nutrition) is indicated to cover the target.

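### The 2% per-patient hypoglycaemia risk used to justify residual risk GR2 holds for about 40 measurements (3.3 days at 2-hourly), yet it is stated without a duration limit for device use of up to 15 days

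*Protocol*

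**What the plan says.** Section 3.7 reports two risks, GR2 and GR3, that are still called unacceptable after mitigation and therefore need justification. For GR2 the justification is that "the expected risk of a patient experiencing hypoglycaemia is 2%, which is smaller than the 5% reported in IIT trials in the control group".

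The 2% is a product of two numbers. The first is the device setting Hypoglycaemia Risk Maximum, 0.05%, defined as follows: "This is the risk that a given BG measurement, made at the due time calculated by GS2, is hypoglycaemic". The second is a count: "Assuming an average of 40 BG measurements per patient, then the patients risk of hypoglycaemia can be estimated as" 0.05% times 40. No source is given for the 40.

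Section 8.1.1, under the calculation of the due time, says that the rule is meant to keep the risk "below the acceptable risk maximum of 0.05% per measurement, or 2% per patient". A parenthesis there repeats the assumption of about 40 measurements on average. The next measurement falls at the GS2 due time or at the time set by local department rules, whichever is sooner.

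On frequency, Section 8.1.2 says of stable glucose: "Then, BG controls should be done every 2 hours". The Synopsis also gives 2-hourly measurement, with closer or extended control depending on stability. Section 8.1.1 expects 2 hours to be the commonest interval for hyperglycaemic patients in the acute phase.

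On duration, Section 7.1 requires an expected stay of at least 72 hours, and the Synopsis says "Glucosafe 2 is used until the patient is discharged from the ICU or for a maximal follow-up of 15 days", or until oral feeding starts.

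**The concern.** A per-patient risk built from a per-measurement risk grows with the number of measurements. The due-time rule controls the first factor and leaves the second free. Under the protocol's formula, any patient with more than 40 measurements is above 2%, so 2% per patient cannot be a maximum that the rule keeps. It is an estimate for one assumed average count.

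That count also looks low beside the trial's own schedule. It is used up in little more than the minimum expected stay, while the device may be used for several times as long.

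At stake is the safety rationale. The 2% is the only figure in the protocol that supports accepting GR2. The trial is the first evaluation of GS2 in humans and has no data safety monitoring committee, so the ethics committee and the authority depend on the written justification.

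**Working it through.** **Inputs.** Risk per measurement p = 0.0005 and count m = 40 (Sections 3.7 and 8.1.1). Interval 2 h, so 12 measurements a day (Synopsis; Section 8.1.2; expected commonest acute-phase interval in Section 8.1.1). Expected stay at least 72 h (Section 7.1). GS2 use up to 15 days (Synopsis). Comparator 5% (Section 3.7).

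**Step 1: reproduce the stated figure.** Protocol formula: m × p = 40 × 0.0005 = 2.00%. Independence form: 1 − (1 − 0.0005)^40 = 1.98%. The 2% reproduces; the multiplication is correct.

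**Step 2: convert 40 measurements to time.** 40 × 2 h = 80 h = 3.33 days.

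**Step 3: the same formulas by days on GS2, at 12 measurements a day.**

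| Days | m | m × p | 1 − (1 − p)^m |
|---|---|---|---|
| 3 | 36 | 1.8% | 1.8% |
| 3.33 | 40 | 2.0% | 2.0% |
| 5 | 60 | 3.0% | 3.0% |
| 7 | 84 | 4.2% | 4.1% |
| 8.33 | 100 | 5.0% | 4.9% |
| 10 | 120 | 6.0% | 5.8% |
| 15 | 180 | 9.0% | 8.6% |

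**Step 4: where 5% is reached.** Product form: 0.05 / 0.0005 = 100 measurements, and 100 / 12 = 8.3 days. Independence form: ln(0.95) / ln(0.9995) ≈ 103 measurements, about 8.5 days.

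**Step 5: sensitivity of the 15-day figure to the interval.** The protocol gives no figure for extended control, so these intervals are assumptions.
- 3-hourly: 120 measurements, 6.0% (5.8% under independence).
- 4-hourly: 90 measurements, 4.5% (4.4%).
- The predecessor's rate in the randomised pilot of Section 3.3.3: 170 / 0.76 ≈ 224 values in 6 patients over 4 days (taking all six as observed throughout) ≈ 9.3 a day. Over 15 days that is about 140 measurements, 7.0% (6.8%).

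**Step 6: what the average could be.** The product form is linear, so the average risk is p times the mean count. Assumed mean use of 5 to 8 days at 2-hourly gives 60 to 96 measurements, or 3.0% to 4.8%. That is above 2% and below 5%.

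**Step 7: how close to the ceiling the measurements would be.** The 0.05% applies at the GS2 due time; a measurement brought forward by the local rule carries less. By the uncertainty-curve formula in Section 8.1.1, the GS2 due time is exactly 2 h when predicted glucose at 2 h equals threshold × exp(3.29 × error). That section gives no value for the threshold, so I assume the 3.2 mmol/l of Section 5.4.
- At the maximum acceptable 2-hour error of 26%: 3.2 × exp(0.855) ≈ 7.5 mmol/l.
- At 17%, the low end of the predecessor's range in Section 3.3.1: 3.2 × exp(0.559) ≈ 5.6 mmol/l.

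Below these values GS2 itself calls for a measurement within 2 h, at the full 0.05%. Above them the local 2-hour rule comes first and the risk is smaller. With an error near the limit, about 12 measurements a day at the full 0.05% is therefore realistic over much of the 5.0 to 8.5 mmol/l target range. With a smaller error the figures in Step 3 overstate the risk more.

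**The case against.** The strongest reply is that nothing has been miscalculated. Section 3.7 gives an expected risk for an average of 40 measurements, and Section 8.1.1 repeats that condition in a parenthesis. The 9% belongs to a patient who stays the full 15 days. Setting that maximum against an average does not show the average to be wrong. This stands. A reader might infer that the expected risk in the trial exceeds 5%, but that would need a mean above about 100 measurements, and the documents give no mean time on GS2.

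Three further points also stand. Measurements made before the GS2 due time carry less than 0.05%, so 9% is an upper-end value; the 2% rests on the same ceiling. Control may be extended in stable patients, so 12 a day is not a floor, and 4-hourly measurement keeps the 15-day figure below 5%. The 72-hour criterion concerns expected stay, not time on GS2: use starts after screening and consent and may end with oral feeding. An average of 40 is therefore unsupported rather than disproved.

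Two other inferences are tempting but lack support. One is that observed hypoglycaemia will be judged against the 2%. No section does this: hypoglycaemia is a safety outcome (Section 5.4), groups are compared with each other (Section 11.4.1), and the early-termination criterion in Section 2.9 counts patients with two severe episodes. The other is that the 40 comes from the predecessor's four-day pilot, where 224 / 6 ≈ 37 values per patient. No passage links them, and the risk management report is not shown.

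The reply does not rescue the wording in Section 8.1.1. The parenthesis states an average, but the sentence offers 2% per patient as a maximum to be kept, and an average count cannot yield a ceiling for each patient. Nor does it supply a duration limit for the comparison with 5% in Section 3.7.

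**Conclusion.** The point holds as a defect in the stated safety rationale. The due-time rule limits the risk per measurement to 0.05%; it does not limit the risk per patient to 2%. By the protocol's own formula at 2-hourly measurement, the per-patient figure is 1.8% at 3 days, 4.2% at 7, 5% at about 8.3 and 9% at 15 (8.6% under independence).

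These figures assume the full 0.05% at every measurement and an unchanged 2-hour interval, so they lie at the upper end. At an assumed 4-hourly interval throughout, the 15-day figure is 4.5%, below 5% but still more than twice 2%.

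It is not shown that the average risk in the trial exceeds 5%. What is not supported for longer stays is an unqualified 2% and an unqualified claim to be smaller than 5%. The follow-up and the definition of hypoglycaemia behind the 5% are not stated either, so the comparison is not clearly like for like in either direction. Sample size, primary outcome and planned analyses are unaffected.

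**What to change.** In Sections 3.7 and 8.1.1:
- Give the basis for the average of 40 measurements, or revise it to fit the 2-hourly schedule, the expected stay and the 15-day maximum.
- State the risk as a function of the number of measurements or days on GS2 up to 15 days (for example at 3, 7 and 15 days), with the assumed interval, and say that it is an upper-end value.
- Remove 2% as a per-patient maximum in Section 8.1.1, leaving 0.05% per measurement as the quantity that the rule controls.
- Limit the comparison with 5% in Section 3.7 to the exposure for which it holds.
- Reconcile the GR2 justification, here and in the risk management file, with the restated figures.

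The cost is wording in two sections and the risk file, and a stated risk that is less favourable. No procedure, sample size or analysis changes.
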